#### Primary outcome

Multivariable logistic regression will be used to simultaneously assess the effects of the three randomized interventions, low-dose dexamethasone (vs placebo), intensive intra-operative glucose control (vs conventional) and light anesthesia (vs deep), on the primary outcome. We will first assess the 3-way and 2-way interactions among the interventions. In absence of interactions, main effects will be assessed by collapsing over the other interventions. Otherwise, the main effects will be assessed within levels of the interacting factors.

#### CRP

A linear mixed effects model (random subject, fixed interventions and time) will be used to assess the effects of the three interventions on CRP at the 1^st ^and 2^nd ^postoperative days, adjusting for baseline. In addition, the association between CRP (each time, plus change from baseline) and outcomes of interest will be assessed using logistic regression, adjusting for intervention.

#### All-cause mortality

Multivariable Cox proportional hazard survival models will be used to assess the relationship between the interventions and all-cause mortality, comparing groups on overall and 12-month survival.

#### Additional outcomes

Time-to-event outcomes (e.g., time to death, hospital LOS, and ICU LOS) will be analyzed using Cox regression, while binary outcomes (e.g., minor perioperative complication composite (Table 2), delirium, and PONV) will be analyzed using logistic regression, and continuous variables (including SF-12) using linear regression or a non-parametric alternative. Additional analyses will be performed adjusting for any baseline potentially confounding factors for which clinical imbalance between randomized groups is observed. The significance level will be 0.05 for all main effect hypotheses, and 0.10 for interactions. Table 3 summarizes the timing of interventions and outcomes' measures.

**Table 2 T2:** Minor Complications

Complication	Requirements for acceptance
Superficial incisional surgical site infection, or hematoma	Surgical evacuation of hematoma and or CDC
Intra-operative ST segment ischemia	An ischemic episode is defined as an ST segment change showing either ≥ 1 mm depression or ≥ 1.5 mm elevation from baseline
Unplanned ICU admission	Unplanned ICU admission
Minor surgical intervention	Surgeon called for care issues during the first 2 hours postoperatively
Non-ventricular arrhythmias	ECG changes, medical Rx and/or electroconversion
Small peritoneal/pleural effusion	Diagnosed by X-Ray, ultrasound, and/or aspiration, and not requiring chest tube, surgery, or ICU admission
Ileus	Lasting more than 72 hours
DVT	Diagnosed by Doppler examination, venogram, or CT scan
Cystitis or urinary tract infection	Fever, dysuria and positive urine culture
Hemodynamic disturbances	Requiring vasoactive drugs and/or β blocker treatment in the first 2 hours postoperatively
Progressive renal insufficiency	Rise in creatinine of > 2 mg/dl from pre-operative value but with no requirement for dialysis

CDC = Center for Disease Control; ICU = Intensive Care Unit; DVT = Deep Venous Thrombosis; Rx = treatment; ECG = Electrocardiogram; CT = Computed Tomography

**Table 3 T3:** Flow -chart of timing of the interventions and outcomes measures

	Pre-op visit	Preop Immediate	Intra-op	Post-op immediately	POD1	POD2	POD3	Hospitalization	30-day	6, 12 months
		Dexamethasone (8 mg)			Dexamethasone (4 mg)	Dexamethasone (2 mg)				
	
**Interventions**			Depth of Anesthesia							
	
			Glucose Control	Glucose Control						

										

								Composite Primary outcome	Primary outcome (mortality)	
	
								Secondary outcomes	Secondary outcomes	Secondary outcomes
	
	SF-12								SF-12	
	
**Outcomes**	Christensen Fatigue Score				Christensen Fatigue Score		Christensen Fatigue Score			
	
					CAM ICU - twice daily	CAM ICU - twice daily	CAM ICU - twice daily			
	
									Phone call- vital status	Phone call- vital status
	
	EKG			EKG	EKG					
	
				Cardiac Enzymes 3 × 8 hrs apart						
	
		CRP			CRP	CRP				

POD = post operative day; SF 12 = health-related quality of life measure; CRP = C-Reactive Protein; CAM ICU =Confusion Assessment Method-ICU

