### Secondary hypotheses

each intervention reduces circulating concentrations of the inflammatory marker CRP; CRP concentration correlates with post-operative complications; anesthetic sensitivity predicts major and minor complications, including delirium. Other secondary hypotheses are that each intervention reduces minor surgical complications, reduces PONV, reduces postoperative delirium, speeds hospital discharge, improves quality of life (SF-12v2 Health Survey, Christensen's VAS fatigue score), and reduces all-cause one-year mortality.

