We will use the Confusion Assessment Method (CAM) as it is the most commonly used tool in the study of delirium. It is easily performed, has a sensitivity of 94% to 100% and a specificity of 90% to 95%[40]. Christensen's fatigue VAS [41] is one of the most widely used measures of postoperative fatigue. The test will be administered pre-operatively and on post-operative days 1 and 3. An increase of three or more units on the 10- point scale will be considered a clinically significant increase.

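### SF-12 and fatigue are scored before surgery, but no baseline term is prespecified for them and adjustment is described only as an extra analysis when imbalance is seen

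*Protocol article*

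**What the plan says.** All references are to the protocol article.

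- **Role of the outcomes.** Under Secondary hypotheses, each intervention is expected to improve quality of life, with SF-12v2 and the Christensen fatigue VAS as the measures.
- **Timing.** For fatigue, Measurements says: "The test will be administered pre-operatively and on post-operative days 1 and 3". Table 3 shows the "Christensen Fatigue Score" at the same three times, and SF-12 at the pre-operative visit and at 30 days.
- **Fatigue criterion.** Measurements adds: "An increase of three or more units on the 10- point scale will be considered a clinically significant increase".
- **Analysis.** Additional outcomes gives "continuous variables (including SF-12) using linear regression or a non-parametric alternative". SF-12 is named and fatigue is not. No covariate is listed.
- **Adjustment rule.** The next sentence of that section reads: "Additional analyses will be performed adjusting for any baseline potentially confounding factors for which clinical imbalance between randomized groups is observed".
- **Comparator.** The CRP section plans a linear mixed model for "CRP at the 1^st ^and 2^nd ^postoperative days, adjusting for baseline".
- **Stratification.** Study Protocol says that randomisation is stratified by history of diabetes.

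**The concern.** SF-12 has the same structure as CRP: one value before the intervention and a later value to be compared across three randomised factors. Fatigue is closer still, with two postoperative days. For CRP the article states the baseline adjustment. For the other two it does not, and the only adjustment rule it gives depends on whether an imbalance is observed.

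That rule is a weak basis for choosing covariates, for two reasons. The precision gained from a prognostic baseline score does not depend on imbalance, so adjusting only after imbalance forgoes the gain in most cases. And a model whose covariates are settled after the baseline comparison has been seen is not fully prespecified. What is at stake is the width of the confidence intervals for the quality-of-life and fatigue comparisons, and how far those estimates move with chance baseline differences.

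**Working it through.** **The plan's own figure.** The article gives no sample size, standard deviation, target difference or correlation for SF-12 or fatigue, so there is nothing to reproduce. The 970 under Sample size considerations was set for the primary composite. It enters here only as the number of patients, about 970 / 2 = 485 per level of each factor if allocation is 1:1 and all patients are analysed.

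**Assumption.** The correlation rho between the pre-operative and follow-up score is not in the document. I take 0.3, 0.5 and 0.7 as a range, and equal variances at the two times.

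**Formulas**, as variances relative to an analysis of the follow-up score alone (= 1):

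- baseline as covariate: 1 − rho²
- change score: 2(1 − rho)
- covariate against change score: (1 − rho²) / [2(1 − rho)] = (1 + rho) / 2
- follow-up-only sample carrying the same information as 970 adjusted patients: 970 / (1 − rho²)

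| rho | Covariate | Change score | Covariate / change | Equivalent N | Gain in N |
|---|---|---|---|---|---|
| 0.3 | 0.91 | 1.40 | 0.65 | 1066 | 10% |
| 0.5 | 0.75 | 1.00 | 0.75 | 1293 | 33% |
| 0.7 | 0.51 | 0.60 | 0.85 | 1902 | 96% |

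The variance therefore falls by 9%, 25% or 49% against the follow-up score alone, and by 35%, 25% or 15% against a change score.

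**On the scale of detectable effects.** With 485 per level, two-sided 0.05 and 90% power, the follow-up-only analysis detects (1.960 + 1.282) × √(2/485) = 0.208 SD. Multiplying by √(1 − rho²) gives 0.199, 0.180 and 0.149 SD. For a difference of 0.18 SD, power is 80% without the baseline score and 84%, 90% or 98% with it.

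**The passages side by side.** CRP has a named model with a baseline term. SF-12 has a named class of model with no covariates listed, followed by adjustment as an additional, imbalance-driven step. Fatigue has a threshold defined on an increase, which uses the pre-operative value, but no model of its own.

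**The case against.** The strongest reply is that the article does not say baseline is left out. The sentence is a one-line summary covering time-to-event, binary and continuous outcomes. It does not list even the three interventions as regressors, and nobody would infer that they are omitted. Linear regression can carry the pre-operative score, and a covariate list is commonly left to the full protocol or SAP, which are not shown. This stands as far as it goes: a reader might infer that the plan commits to an analysis without the baseline value, and the document does not support that. What remains is that the article does address adjustment for these outcomes, and the rule it gives is data-dependent.

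Three further replies stand:

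- **Fatigue.** The three-unit criterion is a change from the pre-operative value, so baseline is not ignored. It is, however, a dichotomised change offered as a mark of clinical significance, not a prespecified model.
- **The non-parametric alternative.** A reader might infer that it must drop baseline. The method is not specified, and a rank test on change scores or a baseline-adjusted rank method would both use it.
- **Size.** No correlation is given, and the comparator could be a change score instead of the follow-up score alone. At rho = 0.7 the gain would then be 15% and not 49%.

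The imbalance rule also partly answers the worry about chance differences, since an imbalanced baseline score could be adjusted for under it.

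**Conclusion.** The point holds as a low-severity gap in prespecification. Both scores are collected before surgery, no baseline term is prespecified for them, and the adjustment that is described waits on observed imbalance, although the same article adjusts CRP for baseline outright.

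The possible gain runs from modest (9% of variance at rho = 0.3, against the follow-up score alone) to substantial (49% at rho = 0.7). All of these figures rest on assumed correlations and on which analysis would otherwise be used; the change-score comparison also assumes equal variances.

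A reader might infer biased quality-of-life estimates or an effect on the trial's main conclusion. Neither follows. Under randomisation, leaving out a baseline covariate costs precision and causes no systematic bias. The primary analysis and the 970 are untouched.

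**What to change.** Prespecify the following in the analysis plan, and align the article's wording if the SAP already says so:

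1. Analyse 30-day SF-12 scores by linear regression on the three interventions, with the pre-operative SF-12 score and history of diabetes (the stratification factor) as covariates.
2. Analyse fatigue on days 1 and 3 with the same type of repeated-measures model as CRP, adjusted for pre-operative fatigue. The three-unit increase can stay as a responder summary.
3. State that any rank-based alternative also adjusts for the pre-operative score.
4. Keep the imbalance-driven analyses as sensitivity analyses only.

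The cost is a few sentences. No new measurement, visit or patient is needed.

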### Interim Monitoring Plan and Adaptive Design Options

The first stage of the study will be a traditional (i.e., non-adaptive) group sequential design[44,45], where interim analyses for both efficacy and futility will be conducted after 25%, 50% and 75% of the patients have been enrolled, and at the end of planned enrollment, as needed. Interventions with either a large or very small treatment effect will likely cross boundaries for efficacy or futility, respectively, at one of the interim analyses, and be stopped early. By the final analysis (including a possible adaptive stage, as explained below), all of the interventions will have either crossed an efficacy or futility boundary.

#### Interim Monitoring Details

We will use the gamma spending function[46] to monitor efficacy (gamma = -3, similar to O'Brien-Fleming) and futility (gamma = 0, similar to Pocock), spending Type I error, which monitors efficacy, slower than the Type II error, which monitors futility, in order to facilitate early stopping for either, but more so for futility (Figure 1). P-values for crossing efficacy (futility) boundaries for the 1^st^, 2^nd^, 3^rd ^and final analyses will be ≤ 0.003 (> 0.972), ≤ 0.007 (> 0.936), ≤ 0.017 (> 0.526) and ≤ 0.041 (> 0.041), respectively, for the 3 interim looks and final analysis of the initial group sequential stage (Figure 2). The overall significance level of 0.05 and power of 0.90 will be maintained. Interim results, along with a recommendation on whether to continue any or all interventions, will be given to the study's Executive Committee which will determine whether to halt or continue the trial at each juncture.

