**Figure 1 F1:**
[figure not shown]
**Spending functions for alpha or type I error (on left vertical axis) and beta or type II error (on right vertical axis) as a function of information time on horizontal axis, where information time is the proportion of the maximum planned sample size available for a particular interim analysis. **Lines represent the cumulative error spent throughout the trial. Beta is spent faster than alpha to allow the study to stop early more readily for futility than for efficacy. Lines are continuous, allowing flexibility in choice of monitoring times, but interim monitoring will only be done at the pre-specified times for this study.

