**Figure 2 F2:**
[figure not shown]
**Stopping boundaries for efficacy and futility. Plot of the standardized treatment effect (z- statistic) on vertical axis and accrued sample size on the horizontal axis, where a z-statistic of zero indicates no treatment effect. **Outside shaded regions indicate sufficient evidence to reject null hypothesis for efficacy (top) or harm (below), while inside shaded region indicates evidence to stop for futility, or no effect.

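### The printed interim futility p-values do not follow from the stated gamma = 0 beta-spending function and delay futility stopping

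*Protocol article*

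**What the plan says.** The protocol article, under Interim Monitoring Plan and Adaptive Design Options, sets the timing: "interim analyses for both efficacy and futility will be conducted after 25%, 50% and 75% of the patients have been enrolled", plus a final analysis. It adds that an intervention with a very small effect will probably cross a futility boundary at one of the interim looks.

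Interim Monitoring Details says the gamma family will be used "to monitor efficacy (gamma = -3, similar to O'Brien-Fleming) and futility (gamma = 0, similar to Pocock"), with type I error spent more slowly than type II error so that stopping is easier for futility than for efficacy. It lists the efficacy p-values, with futility p-values in brackets, as "≤ 0.003 (> 0.972), ≤ 0.007 (> 0.936), ≤ 0.017 (> 0.526) and ≤ 0.041 (> 0.041"), and states: "The overall significance level of 0.05 and power of 0.90 will be maintained".

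The Figure 1 legend repeats the intent: "Beta is spent faster than alpha to allow the study to stop early more readily for futility than for efficacy". The Figure 2 legend describes efficacy and harm as outer regions, "while inside shaded region indicates evidence to stop for futility, or no effect". The design is therefore two-sided, with an inner futility wedge around z = 0.

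**The concern.** The look times, the two gammas, alpha, power and the shape of the futility region fix the boundaries. The printed futility cut-offs look far too strict for linear beta spending: at half of enrolment an intervention would need p above 0.936, that is |z| below 0.08, to be called futile.

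The cut-offs inform the recommendation to the Executive Committee on each intervention, and the two rules can disagree. An intervention with p = 0.70 at 50% enrolment meets the futility criterion under the stated function and does not under the printed one. At stake are how long an ineffective intervention goes on being tested and how many patients that takes.

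**Working it through.** **Inputs.** Two-sided alpha 0.05, beta 0.10, gamma = -3 and gamma = 0 (Interim Monitoring Details); information times t = 0.25, 0.50, 0.75, 1 (Interim Monitoring Plan); inner-wedge futility region (Figure 2 legend). No event rate is needed for steps 1 to 4.

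**1. Reproduce the efficacy values.** The fraction of alpha spent by time t is (1 − e^(−γt)) / (1 − e^(−γ)). With γ = -3 this is 0.0585, 0.182, 0.445 and 1, so cumulative alpha is 0.0029, 0.0091, 0.0222 and 0.05. Recursive integration, ignoring the futility boundary (non-binding), gives |z| = 2.975, 2.694, 2.383, 2.044 and p = 0.0029, 0.0071, 0.0172, 0.0409. All four printed values match. A binding futility rule would give 0.0518 at the final look, so the printed 0.041 points to the non-binding form.

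**2. Futility values from gamma = 0.** Cumulative beta is linear: 0.025, 0.050, 0.075, 0.100. Solving for the drift at which the boundaries meet at the final look gives 3.568.

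| Look | Printed p (abs. z) | Gamma = 0 p (abs. z) |
|---|---|---|
| 1 | > 0.972 (0.035) | > 0.879 (0.15) |
| 2 | > 0.936 (0.080) | > 0.517 (0.65) |
| 3 | > 0.526 (0.634) | > 0.165 (1.39) |
| Final | > 0.041 (2.04) | > 0.041 (2.04) |

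Using a drift of 3.559 instead (N = 970 under the assumption in step 5) gives 0.880, 0.521 and 0.167.

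**3. Beta spent by the printed cut-offs.** This can be checked by hand. At drift 3.568 the mean of z at look k is 3.568 × √t.
- Look 1: mean 1.784; P(|z| < 0.035) ≈ 2 × 0.0351 × φ(1.784) = 0.0702 × 0.0812 = 0.0057.
- Look 2: mean 2.523; P(|z| < 0.080) ≈ 2 × 0.0803 × φ(2.523) = 0.1606 × 0.0166 = 0.0027.
- Look 3: mean 3.090; P(|z| < 0.634) = Φ(−2.456) − Φ(−3.724) ≈ 0.0070 − 0.0001 = 0.0069.

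These ignore stopping at earlier looks, so their sum, 0.0153, is an upper limit on beta spent by look 3. The stated function spends 0.075. The exact cumulative values are 0.0057, 0.0083 and 0.0143 (0.0058, 0.0084 and 0.0146 at drift 3.559).

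| Look | Beta spent, printed | Beta spent, gamma = 0 | Alpha spent, gamma = -3 |
|---|---|---|---|
| 1 | 6% | 25% | 6% |
| 2 | 8% | 50% | 18% |
| 3 | 14–15% | 75% | 44% |

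Even at the drift where the printed rule itself has exactly 90% power (3.332), it spends only 0.0070, 0.0108 and 0.0213, that is 7%, 11% and 21%.

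Other conventions do not rescue the printed triple. Beta gammas from 1 to -6, binding futility, and one-sided designs at 0.025 and 0.05 all fail. Gamma = -3 comes close at look 1 only (0.976, 0.795, 0.275).

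**4. Operating characteristics.** The gamma = 0 column uses the boundaries at drift 3.559; those at 3.568 give 12%, 53%, 86% and 596.

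| | Printed | Gamma = 0 |
|---|---|---|
| Cumulative futility stop, no effect, looks 1/2/3 | 2.8% / 8.9% / 50% | 12% / 52% / 86% |
| Expected N of 970, no effect | 811 | 598 |
| Power where the stated rule has about 90% | 0.93 | 0.90 |

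The look 1 stopping rates are simply 1 − 0.972 = 0.028 and 1 − 0.88 = 0.12. Overall alpha with the printed boundaries is 0.049, or 0.050 if futility crossings are ignored. At a quarter of the design drift (roughly a 10% relative reduction), cumulative futility stopping by look 3 is 39% printed against 75% with gamma = 0.

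**5. Supporting check on N.** Sample size considerations gives 25% with no intervention and relative reductions of 40%, 20% and 10%. Assume, since the article does not say so, that the control rate is averaged over the other two factors: 0.25 × 0.90 × 0.95 = 0.214, against 0.6 × 0.214 = 0.128. The fixed-design N is then 804 (unpooled) to 812 (pooled). Multiplying by the inflation (3.568/3.2415)² = 1.2115 gives 975 to 984, within 2% of 970. The printed cut-offs need inflation of only 1.057, giving 850 to 858. Without averaging (25% against 15%, fixed N 662 to 670), gamma = 0 gives 802 to 812 and the printed rule 699 to 708, so neither fits 970.

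**The case against.** The best defence is that nothing inferential is lost. The article promises overall alpha of 0.05 and power of 0.90, and the printed boundaries deliver about 0.049 and 0.93. Interim results go with a recommendation to an Executive Committee that decides, and the efficacy values fit a non-binding rule, so crossing a futility boundary does not by itself drop an intervention. All of that stands, and it limits the consequence to the timing of futility stopping.

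A reader might infer several stronger points that the article does not support:
- **That the trial almost never stops early for futility.** This is fair for looks 1 and 2 (about 9% together under no effect), but about half of null interventions would stop by look 3.
- **That beta is spent more slowly than alpha throughout.** At look 1 the two are level at 6%; the reversal begins at look 2.
- **That Figure 2 is wrong.** The plot is not available in the text reviewed, and its legend agrees with an inner wedge. It may show the right boundaries.
- **That 970 was inflated for a rule not applied.** This depends on the averaged control rate in step 5, which is plausible but not stated.
- **That Additional outcomes conflicts with the final threshold of 0.041.** It says "The significance level will be 0.05 for all main effect hypotheses, and 0.10 for interactions", which reads naturally as the overall level, with 0.041 as its nominal value at the last look. Nothing says the final primary test is run at a nominal 0.05.

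None of this explains the three printed numbers.

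**Conclusion.** The mismatch is real. The three interim futility p-values cannot come from the gamma = 0 function named alongside them, and from look 2 they reverse the stated ordering of beta and alpha spending. Under no effect the printed rule enrols on average about 213 more patients per null intervention than the stated one (811 − 598). This rests only on the article's own alpha, beta, gammas and look times, with a two-sided, non-binding reading that its efficacy values confirm; the event-rate assumption moves the figures only in the last digit or two.

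Validity of the final conclusions is not at risk. Which item is in error, the p-values or the description, cannot be settled from the article. The fit of 970 to gamma = 0 suggests the p-values, but only under the averaging assumption.

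**What to change.** Re-run the design in East, the software the article names, and then do one of two things:
- If gamma = 0 is intended, print the futility p-values it gives (about > 0.88, > 0.52, > 0.17, then > 0.041) in Interim Monitoring Details, and check the Figure 2 boundaries against them.
- If the printed p-values are intended, replace the description "futility (gamma = 0, similar to Pocock") with the function actually used, withdraw the statements there and in the Figure 1 legend that beta is spent faster than alpha, and restate the power.

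The Executive Committee should have one agreed set of futility boundaries before the next interim look. The cost is a software re-run and a short correction to the text, with no extra patients.
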